### Data and safety monitoring board

The data and safety monitoring board (DSMB) for this trial comprises independent experts in statistics and ophthalmology appointed by the trial steering committee. The DSMB will meet biannually in person or virtually as needed to review the progress of the trial. Any modifications to the study protocol will be reviewed by the relevant ethics committees in the UK and Tanzania and the DSMB. The DSMB will also monitor any adverse events that occur during the trial.

### Sample size considerations

This study is powered to test the hypothesis that AI-supported DR screening increases the proportion of persons with true referable DR who attend the central ophthalmology clinic following referral after screening.

Our prior evaluation of the DR screening programme showed that the rate of follow-up for persons referred from screening to the ophthalmology clinic was 42%.^8^ Using this value, and in discussion with our partners in Tanzania, it was agreed that a 33% increase in compliance with follow-up recommendations would be a significant and programmatically meaningful improvement to the service.

Assuming that 22.5% of persons screened have true referable DR, with 1182 persons screened per trial arm (2364 persons in total), and therefore 266 persons with true referable DR in each arm, we would have a 90% power to detect a 33% uplift (from 42% to 56%) in attendance at the ophthalmology clinic for those persons with true referable DR.

### Analysis plan

The analysis will be by intention to treat and all participant data will be analysed according to their randomisation allocation. However, not all participants randomised will be included in all analyses. For example, our primary outcome analysis includes only those persons with true referable DR as defined by the reference standard gradings.

The data will be analysed and reported according to the Consolidated Standards of Reporting Trials (CONSORT) AI extension guidelines for reporting RCTs.^18^ These guidelines are based on the CONSORT 2010 guidelines and have been adapted to produce a set of recommendations for clinical trials evaluating interventions with an AI component.

#### Primary outcome analysis: unadjusted analysis

The primary analysis will be a comparison of the proportion of persons with true referable DR out of all those with true referable DR (determined by the reference standard gradings) who attend the central ophthalmology clinic between the standard of care DR screening pathway (control) and the AI-supported DR screening pathway (intervention). The primary analysis of the primary outcome will be by logistic regression model using attendance at 8 weeks as the binary outcome, trial arm as the exposure and all participants who were classed as having referable DR by the reference standard measure will be included in the analysis. The intervention effect of AI-supported screening will be estimated as an OR with a 95% CI.

#### Primary outcome analysis: adjusted analysis

We will perform an adjusted analysis, adjusting for measured potential confounders including gender, education level and distance from the screening clinic to the referral hospital, to account for any potential imbalance between the arms in terms of measured variables (or associated unmeasured confounders).

As attendance versus non-attendance at the specialist eye clinic for participants with true referable DR is the primary outcome measure, missing outcome data due to loss to follow-up will not be an issue. For example, if an individual enrolled in the trial is referred to the central ophthalmology clinic but does not attend the follow-up appointment, they will be considered a non-attender and will be included in the analysis as such; they will not be considered lost to follow-up.

#### Analysis of other potential determinants for attendance of true referable DR cases at the eye clinic

Logistic regression models will be used to analyse potential factors that may be associated with the primary outcome (attendance of true referable DR cases at the eye clinic). These potential factors include: age, gender, education level, occupation, distance from screening site to referral hospital, type of diabetic clinic (government funded, private, church based), duration of diabetes, visual acuity, type of diabetic treatment (insulin, tablets) and any previous ophthalmic treatments.

We will initially perform a univariable analysis of all variables, followed by a multivariable analysis adjusting for all potential confounders. Both the univariable and multivariable analyses will be presented.

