Major challenges were faced by the KDP as well as other similar programmes in the African region. First, there are not enough skilled eye care staff. Often the same eye care staff screen, follow-up and then treat patients with sight-threatening disease, placing additional pressure on already overstretched systems. The number of eye care staff currently in the African region is already unable to cope with the clinical demands and is very likely to be overwhelmed by the projected surge in demand for diabetic eye care services over the next 30 years. Second, there is limited quality control and training of staff in grading retinal images, and it is therefore unclear how accurate the DR gradings are within the current screening programmes. And third, in the KDP, it was noted that there were poor rates of follow-up (42%) for those referred with potentially sight-threatening DR from screening to secondary eye care.^8^ This meant the KDP was identifying people with potentially sight-threatening DR at risk of sight loss, but less than half of those people attended the central ophthalmology clinic for assessment; this strongly affected the ultimate impact of the programme.

In Tanzania, there is no widely available postal service and particularly older, poorer people have no or limited access to telephones and the internet, making it practically impossible to provide some patients with their results and follow-up advice at a later date. Moreover, through 300 interviews with patients with diabetes registered with the KDP, we found that an understanding that DR can be treated and knowledge of the location of the referral hospital are positively related to adherence to follow-up. The provision of an immediate referral decision with real-time feedback and point-of-screening counselling is likely to improve the rates of follow-up for those referred to the eye clinic with sight-threatening DR.^9 10^

In view of the substantial projected increases in the number of people with diabetes worldwide, particularly in LMICs, there is an urgent need to test, develop and implement effective screening services for DR in order to prevent sight loss from the disease.

An alternative system to screen patients for DR that reduces demands on specialist staff, improves quality control and adherence to follow-up is needed. Advances in artificial intelligence (AI) for healthcare offer a potential alternative.

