### Intervention and standard of care

#### Standard of care

The standard of care is the process by which patients have been screened for DR in the Kilimanjaro DR screening programme for >10 years. After retinal image capture, the photographs will be stored on a laptop and taken back to KCMC Eye Department. The images will be graded by an ophthalmology resident for the level of DR. Persons with referable DR will be contacted by text message or phone call some weeks after screening and advised to attend KCMC Eye Department for assessment with or without treatment. The counselling participants in the standard of care arm receive will follow the same format as the counselling given in the intervention arm of the trial, except that it will be delivered by telephone.

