#### Intervention arm

The intervention in this trial is a complex intervention^13^ including AI-supported retinal image analysis for DR grading with immediate feedback and referral advice followed by point-of-screening patient counselling.

There are two components to the intervention:

AI retinal image analysis and DR grading.Face-to-face counselling at the point of screening.

The use of AI to grade retinal images for DR enables point-of-screening, face-to-face counselling as automated analysis provides immediate feedback after image submission, with a referral decision. The screening team member will inform the participant of their DR grade and proceed with the counselling component of the intervention. The point-of-screening counselling will include an explanation of what DR is, the potential to cause vision loss, the referral process and will emphasise that there are effective and safe treatments for DR.

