#### AI system selection

There are several AI systems commercially available for DR screening.^12^ A review process informed the choice of AI system in this trial.^14^ In summary, the following criteria were considered: existing regulatory approval (FDA approval or CE marking), ability to work offline, evidence of performance in an African population and the ability to work with different cameras. The SELENA+AI software (EyRIS)^15^ was the only system to meet all these criteria and was therefore selected. In a prior published validation study in Zambia the SELENA+AI system had a sensitivity of 92.25% and a specificity of 89.04% for detecting referable DR.^16^

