### Grading of retinal photographs

All retinal images captured in the trial will be graded by (1) the Tanzanian ophthalmology residents, (2) the AI system and (3) UK-certified graders. This will enable comparison of the performance of the AI system versus Tanzanian ophthalmology residents and against a reference standard (UK-certified graders). All graders will be masked to the other DR gradings.

For the reference standard gradings, the UK-certified graders will undertake feature-based grading and the retinal images will be labelled using a software program (OptoMize, NEC Software Solutions, UK) commonly used in the English National Screening Programme. All images will be labelled by two experienced graders from the English National Screening Programme. The graders will only have access to anonymised retinal images with no patient metadata. Any disagreements will be adjudicated by a third senior grader. All graders involved are subject to the English Diabetic Eye Screening quality assurance process.

Participants noted to have any of the following after grading by the UK-certified graders will be defined as having true referable DR: preproliferative, proliferative DR, referable maculopathy or an ungradable retinal image. Referable maculopathy is defined as the presence of hard exudates or blot haemorrhage within 1 disc diameter of the fovea (centre of the retina) or a circinate or group of exudates within the macula. This definition of referable DR and maculopathy follows the Tanzanian National Guidelines for the Management of DR (published by the Tanzanian Ministry of Health) which is the nationally approved standard of care for Tanzania.

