### Outcome measures

#### Primary outcome measure

The primary outcome will be the proportion of persons with true referable DR who attend the central ophthalmology clinic within 8 weeks of screening out of all those with true referable DR (defined by the reference standard), by trial arm.

All retinal images will be graded by UK-certified graders to provide the reference standard. It will be these gradings that will determine which participants have true referable DR in each trial arm and this figure will be the denominator in our primary outcome analysis.

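### The determinants models cover all true referable cases, including those their own pathway did not refer, so their odds ratios mix detection with adherence

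*Protocol article*

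**What the plan says.** The section on other potential determinants fits univariable and then multivariable logistic models for "potential factors that may be associated with the primary outcome (attendance of true referable DR cases at the eye clinic". The factors listed include age, education, distance, duration of diabetes, visual acuity and previous ophthalmic treatment. Trial arm is not named, but the list is open-ended.

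The population is that of the primary outcome: "out of all those with true referable DR (defined by the reference standard), by trial arm". On the UK-certified gradings, the Primary outcome measure section adds: "It will be these gradings that will determine which participants have true referable DR in each trial arm".

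Referral follows a different grade. Under Standard of care the residents grade the images, and then: "Persons with referable DR will be contacted by text message or phone call some weeks after screening". Under Intervention arm, "automated analysis provides immediate feedback after image submission, with a referral decision". The Interim analysis section adds a recall: images that the AI calls non-referable but the residents call referable go to a senior grader, and confirmed cases are contacted. No matching review is described for disease that the residents miss.

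All three gradings will exist for everyone: "All retinal images captured in the trial will be graded by (1) the Tanzanian ophthalmology residents, (2) the AI system and (3) UK-certified graders".

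**The concern.** A person with true referable disease can fail to attend for two reasons: the pathway's grader missed the disease and gave no advice to attend, or the advice was given and not followed. The determinants models code both as the same outcome.

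That is deliberate and sound for the arm comparison, where a missed case is a failure of the pathway. It is less suitable for a section headed as determinants of attendance. Elsewhere the article treats attendance as a response to a referral. Follow-up assessment defines a non-attender as someone recommended to attend who did not. The example under the adjusted analysis is a referred person who does not come. The 42% in the Introduction and the sample size section is a rate among those referred, and Patient and public involvement speaks of adherence to referral.

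Some listed factors could plausibly relate to detection. Longer duration or worse acuity may go with disease that is easier to see. An ungradable image also counts as true referable disease, and image quality may vary with acuity or age. If so, the programme could read a grading problem as a patient problem and aim its counselling or outreach at the wrong group.

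**Working it through.** **The plan's own figure.** 1182 × 0.225 = 265.95, so 266 true cases per arm. For 42% v 56% with 266 per arm, two-sided 5% (assumed, in line with the 95% CI), power is 0.900. The stated 90% reproduces and is not in dispute. It gives 2 × 266 = 532 true cases for the determinants models.

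**How many true cases are not referred by their own grader.** The AI, in a prior validation study, "had a sensitivity of 92.25% and a specificity of 89.04% for detecting referable DR": 266 × (1 − 0.9225) = 21 missed. Resident sensitivity is not given; the Introduction says "it is therefore unclear how accurate the DR gradings are within the current screening programmes". Assuming 80%, 266 × 0.20 = 53 are missed; assuming 60%, 266 × 0.40 = 106.

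**Spurious odds ratio for a factor that affects detection only.** Let s be detection, a attendance if referred, and u attendance if not referred:

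P(attend) = s·a + (1 − s)·u

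Take a = 0.42 and 0.56 (the two attendance rates in the sample size section) and u = 0 and 0.05 (assumed). Neither a nor u depends on the factor, so its odds ratio for adherence is 1.00. All values of s by factor level are assumptions.

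| Detection | a | u | Attendance | Odds ratio |
|---|---|---|---|---|
| 90% v 70% | 0.42 | 0 | 37.8% v 29.4% | 0.685 |
| 90% v 70% | 0.42 | 0.05 | 38.3% v 30.9% | 0.720 |
| 90% v 70% | 0.56 | 0 | 50.4% v 39.2% | 0.635 |
| 90% v 70% | 0.56 | 0.05 | 50.9% v 40.7% | 0.662 |
| 92% v 85% | 0.42 | 0.05 | 39.0% v 36.5% | 0.896 |
| 92% v 85% | 0.56 | 0 | 51.5% v 47.6% | 0.855 |

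For example, row one: (0.294/0.706) / (0.378/0.622) = 0.685. The last two rows are the extremes for 92% v 85%. If detection does not differ by the factor, the odds ratio is exactly 1.00.

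With 532 cases split evenly on the factor, the false association would reach p < 0.05 in 43% to 74% of trials at 90% v 70%, and in 9% to 15% at 92% v 85%.

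**Does leaving out trial arm cause this?** Take attendance if referred of 42% in the control arm and 56% in the AI arm, with u = 0.

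- Detection 90% v 70% in both arms: odds ratio 0.662 without arm, 0.658 with arm.
- Detection 90% v 70% in the control arm only, AI at 92.25% throughout: 0.842 without arm, 0.837 with arm.
- A factor with a genuine within-arm odds ratio of 2.0: 1.97 without arm. A true value of 1 stays at 1.00.

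Arm is randomised and so is independent of baseline factors. Adding it leaves the detection artefact almost unchanged.

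**The case against.** The strongest defence is that the section claims only association with the primary outcome, and that outcome is a pathway-level one by design. Read that way, the model is coherent. The secondary analyses also report attendance among those referred and the sensitivity of both graders. This stands as a reason to keep the planned model. It does not remove the difficulty, because those secondary results are given by arm and not by patient factor, and the section's heading invites the reading that the factors explain attendance.

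Several stronger readings are tempting, and the documents do not support them.

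- *That missed cases are never told to attend.* Some AI misses are recalled under the Interim analysis section.
- *That omitting trial arm produces the artefact.* It does not, as shown above. Nor is arm excluded: the list is open, the heading says other determinants, and exact covariates may be left to the analysis plan.
- *That detection-related factors will be reported as reasons for attending.* This needs detection to differ materially by a listed factor, and no figure in the article shows that it does.
- *That the artefact is very large.* Detection of 95% v 65% in both arms, with 50% adherence and no attendance otherwise, gives 47.5% v 32.5%, an odds ratio of 1.88. Those rates average 80%, which is hard to square with the AI's quoted 92.25%. If they apply to residents only and the AI has 95% v 89.5% (mean 92.25%), pooled attendance is 47.5% v 38.6%, an odds ratio of about 1.44.
- *That the primary comparison is biased.* Counting missed cases there is intended.

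**Conclusion.** The point holds in limited form. The determinants models cannot separate detection from adherence, so a factor related to detection can appear as a determinant of attendance. Under the assumed rates the spurious odds ratio is about 0.63 to 0.72 for detection of 90% v 70%, and about 0.85 to 0.90 for 92% v 85%. The second would seldom be noticed; the first often would. These figures rest on assumed detection rates by factor, an unknown resident sensitivity, and 0% to 5% attendance without referral.

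This concerns an exploratory analysis outside the listed primary and secondary outcomes. It is worth correcting because the correction is cheap and the result is likely to be read as advice on why patients do not come.

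**What to change.** Keep the planned model in all true referable cases, and describe it as a pathway-level association with the primary outcome.

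Add the same model in true referable cases that both the AI and the residents graded referable, and interpret this one as determinants of attendance among people due to be referred. Both grades exist for every participant, so membership of the set does not depend on arm. Restricting instead to those referred in their own arm would make it depend on arm.

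Name trial arm as a covariate in both models, for precision. Arm-by-factor terms are optional and exploratory; they would be imprecise in a set of this size.

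The cost is analysis-plan wording and a smaller set. With sensitivities of 92% and 80% (the latter assumed) and independent misses, 532 × 0.92 × 0.80 gives about 390 of 532. The set leans towards more readily detected disease. Some control participants in it may still not be reached by telephone, a limit that the Introduction itself acknowledges, so the result should be described as applying to those due to be referred and not to those known to have been told.

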### Eligibility criteria

Potential participants will need to meet the eligibility criteria stipulated in table 1. In summary, potentially eligible participants include all persons aged over 18 years with diabetes in the Kilimanjaro or Arusha regions of Tanzania and who attend a diabetic clinic, which is where DR screening occurs. The eligibility criteria are broad to reflect the reality of DR screening in Tanzania.

**Table 1 T1:** Inclusion and exclusion criteria for enrolment into the randomised controlled trial

Inclusion criteria	Exclusions criteria (any of the following)
1. Adult (18 years and older) living with diabetes and attending diabetes clinics in Kilimanjaro or Arusha region.	1. Unable or unwilling to consent.
2. Willing and able to give consent.	2. Less than 18 years old.
3. Agree to be randomised to either AI-supported or standard of care DR screening.	3. Already attending the central ophthalmology clinic or had a diabetic eye examination in the previous 12 months.

AI, artificial intelligence; DR, diabetic retinopathy.

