### Randomisation

#### Randomisation sequence

A computer-generated randomisation list will be prepared by a statistician at London School of Hygiene & Tropical Medicine (LSHTM). The sequence will be in a 1:1 allocation ratio of standard DR screening to AI-supported DR screening, blocked with a random block size of 4–8.

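### In the determinants analysis, two factors vary only between clinics but the stated logistic model has no clinic term, so their intervals will be too narrow if attendance clusters by clinic

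*Protocol article*

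**What the plan says.** In the Protocol article, the section on other potential determinants of attendance names the method: "Logistic regression models will be used to analyse potential factors that may be associated with the primary outcome". It names the sequence: "We will initially perform a univariable analysis of all variables, followed by a multivariable analysis adjusting for all potential confounders". It also names the candidate factors. Some are personal: "These potential factors include: age, gender, education level, occupation", followed later in the list by duration of diabetes, visual acuity and treatment history. Two belong to the clinic: "distance from screening site to referral hospital, type of diabetic clinic (government funded, private, church based").

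The adjusted primary analysis confirms where distance is measured from: "distance from the screening clinic to the referral hospital". It is therefore not the distance from the participant's home.

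Participants are people "attending diabetes clinics in Kilimanjaro or Arusha region", so there are several clinics, but their number is not given. Allocation is individual and "blocked with a random block size of 4–8", with no stratification by clinic stated. The article does not mention correlation within clinics, a clinic effect or robust standard errors, either to include or to exclude them.

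**The concern.** A factor that is constant within a clinic can be studied only by comparing clinics. People screened at the same site share its staff, transport links, local economy and referral habits, so their attendance may be more alike than that of people from different sites. Logistic regression without a clinic term treats each person as an independent observation of distance and clinic type, and so credits the data with more information on these factors than they hold.

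The protocol's own list points to such correlation. Distance and clinic type are included because each may affect attendance. If one of them does, the univariable model for the other leaves that between-clinic variation unmodelled, and the univariable results are to be presented.

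What is at stake is a secondary reading of the trial. A contrast driven by a few clinics could be reported as a determinant of attendance with more confidence than the data support. The treatment comparison is not at stake.

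**Working it through.** **Inputs from the article**
- True referable cases: "therefore 266 persons with true referable DR in each arm", so 2 × 266 = 532 in the determinants models.
- Attendance: 42% against 56%, with 90% power.
- Confidence level: 95% for the primary effect. A two-sided 5% level is assumed throughout.

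**Reproducing the plan's figure**
- n per arm = [1.960 × √(2 × 0.49 × 0.51) + 1.282 × √(0.42 × 0.58 + 0.56 × 0.44)]² / 0.14² = 266 after rounding up. Power at 266 per arm is 0.900.
- 1182 × 0.225 = 265.95, or 266. The stated figure holds.

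**Inputs that must be assumed**
- The article gives neither the number of clinics K nor the ICC. The ranges used are K = 10, 20, 40 (equal sizes) and ICC = 0.01, 0.02, 0.05.
- As a guide to scale only: if clinics were split evenly between 42% and 56% attendance, the between-clinic variance would be 0.07² = 0.0049. The total variance is 0.49 × 0.51 ≈ 0.25, so the ICC would be about 0.02.

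**Formulas for a factor constant within clinic**
- Cases per clinic: m = 532 / K
- Design effect: DE = 1 + (m − 1) × ICC
- Factor by which the interval should be wider: √DE
- Actual coverage of the nominal 95% interval: 2Φ(1.96 / √DE) − 1

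Example, K = 20 and ICC = 0.02: m = 26.6; DE = 1 + 25.6 × 0.02 = 1.51; √DE = 1.23; coverage = 2Φ(1.59) − 1 = 89%, so a nominal 5% test runs at about 11%.

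**Check by simulation.** There were 1000 runs per setting, with random clinic intercepts on the logit scale and mean attendance near 49%. Logistic regression without a clinic term was fitted with one clinic-level factor, one personal factor and trial arm, none of which had any true effect.

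| Clinics (cases each) | ICC | DE | Width factor | Coverage | Simulated type I error, clinic-level factor |
|---|---|---|---|---|---|
| 10 (53.2) | 0.01 | 1.52 | 1.23 | 89% | 10.6% |
| 10 | 0.02 | 2.04 | 1.43 | 83% | 16.7% |
| 10 | 0.05 | 3.61 | 1.90 | 70% | 27.1% |
| 20 (26.6) | 0.01 | 1.26 | 1.12 | 92% | 7.5% |
| 20 | 0.02 | 1.51 | 1.23 | 89% | 10.9% |
| 20 | 0.05 | 2.28 | 1.51 | 81% | 16.1% |
| 40 (13.3) | 0.01 | 1.12 | 1.06 | 94% | 6.6% |
| 40 | 0.02 | 1.25 | 1.12 | 92% | 6.8% |
| 40 | 0.05 | 1.62 | 1.27 | 88% | 12.3% |

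In the same nine settings, type I error was 4.0% to 5.5% for the personal factor and 4.1% to 5.4% for trial arm, that is, nominal within simulation error. The simulated rates for the clinic-level factor agree with the formula or fall somewhat below it (for example 27% against 30% for 10 clinics at ICC 0.05). At ICC = 0, DE = 1 and there is no error.

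**The case against.** The strongest reply is that the article does not rule out a clinic term. Mixed-effects logistic regression, and logistic regression with cluster-robust errors, are both logistic regression models, and a variance method can be left to an analysis plan that is not shown. This stands in part. The article is silent on clustering, so a reader who infers that the authors considered and dismissed it goes beyond the text. The point survives because the article names both a method and covariates, and that method, applied as stated to two of those covariates, understates their uncertainty whenever the ICC is positive.

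Second, the error is conditional. Neither K nor the ICC is known, and in the multivariable model the relevant ICC is what remains after adjustment, which may be smaller than the crude value. This stands: the table gives a range, not an estimate.

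Third, a reader might infer that every interval in these models is too narrow, or that the primary comparison is affected. Neither follows. Personal factors spread evenly across clinics and the individually randomised arm effect kept their nominal error rate. In the adjusted primary model, distance is only an adjustment variable and the estimate of interest is trial arm, so there is no shown need for a change. A random intercept there would also make the adjusted odds ratio clinic-specific and less comparable with the unadjusted one.

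Fourth, the determinants analysis appears in neither the objectives nor the listed outcomes. This stands, and it limits the weight of the point.

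**Conclusion.** The point holds in a limited form and is minor. As stated, the determinants models would give intervals that are too narrow for distance and for clinic type if attendance is correlated within clinics. Under the assumed range of 10 to 40 equal-sized clinics and an ICC of 0.01 to 0.05, these intervals should be 1.06 to 1.90 times as wide, and a nominal 95% interval would cover the truth about 70% to 94% of the time. The low end is negligible and the high end is not; the article does not show where the trial lies. The conclusion on trial arm is untouched. If the analysis plan already specifies a clinic effect or clustered variance for these models, nothing remains to change.

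**What to change.** In the determinants models, univariable and multivariable, that include distance or clinic type, use either a random intercept for screening clinic or cluster-robust standard errors by clinic with a small-sample correction. Report the number of clinics with the results. Do not use clinic fixed effects, which would absorb both factors and leave nothing to estimate. Leave the unadjusted and adjusted primary arm comparisons as planned.

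The cost is about one sentence in the analysis plan. Table 2 of the article does not list clinic as a data item, but clinic must be identifiable because both factors are derived from it. The downside is wider intervals for these two factors. With a random intercept, the odds ratios in these models are also read as clinic-specific.
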